#### Sub-group analyses

We will undertake exploratory sub-group analyses to assess evidence for whether the effect of the intervention varies according to age, entertainment venue, level of education, and socioeconomic status. If statistically significant, overall heterogeneity is identified, then relative risks and 99% confidence intervals will be estimated.

#### Additional analyses

We will provide a descriptive analysis of information on study-related mobile phone use among participants. The aim will be to include number of voice message and phone interactions, response to voice messages, response to weekly surveys, time spent on phone calls, and linkages to outreach workers to facilitate description of process indicators and any issues. Additionally, at the end of the trial, the costs of the intervention (training, human resources, phone costs, and so on) will be estimated.

#### Qualitative interviews

We will conduct around 15 to 20 qualitative interviews (or until data saturation has been reached) with participants who received the intervention. Participants for interviews will be selected purposively to include those who did or did not appear to respond to the intervention. The interviews will explore participants’ experience of the intervention, aiming to identify active components of the intervention, and seek recommendations for improvements. Interviews will be recorded and transcribed and a simple thematic analysis will be undertaken. We will use the findings to inform any adjustments to the intervention after the trial. We will also conduct process interviews with community health workers and outreach workers to better understand the utility and effectiveness of the weekly monitoring survey in their work and explore feasibility of scaling.

### Ethical consideration

The trial will be conducted in accordance with the principles of Good Clinical Practice. The study protocol has been approved by the National Ethics Committee for Health Research (NECHR, No. 142NECHR) of Ministry of Health in Cambodia and Touro College Institutional Review Board (No. PH-0117). The *Mobile Link* trial has been registered with ClinicalTrials.gov (No. NCT03117842).

All participants will provide verbal informed consent before enrolling in the trial or commencing the follow-up interviews. All client records and data will be stored securely. No names of participants (or others mentioned) or locations will be used in the analyses or report writing. Confidentiality will be maintained by assigning coded identifiers to participant names (with a master list stored separately). Participants will be able to withdraw from the study at any point. When withdrawing from the study, the participant would let the research team know that she wishes to withdraw. The participant may provide the research team with the reason for leaving the study, but this is not requirement.

Any participants with an adverse outcome arising from other people listening to VM (for example, an argument or violence) will be linked into appropriate existing services at local organizations. Each survey will ask about experiences with social harms as a result of the study. Social harms experienced by participants and reported to research staff during data collection will be documented and monitored by investigators. Participants will be reimbursed to compensate for expenses related to face-to-face clinic follow-up and for participation in the surveys.

#### Application, dissemination, and transposition of results

This study is a proof of concept. If found to be both effective and cost-effective, replication and rapid scale-up of the intervention can be achieved. The nature of the intervention, SMS/VM interactions, can be easily modified using the existing digital platform developed for this trial to accommodate more users from the same population after performing outreach and enrolment. In order to serve users from a different population, we would need to conduct qualitative work to develop new tailored high-quality theory-informed messages and conduct the initial outreach and enrolment activities. The results of this study will be shared at local, regional, and international levels. We will collaborate with national institutions, such as the National Center for HIV/AIDS, Dermatology and STD (NCHADS), the National AIDS Authority, and the National Institute of Public Health (NIPH) in Cambodia, who will be aware of and involved in this project, to disseminate the information about this study locally. We would plan to host a regional meeting with stakeholders from neighboring countries, such as Laos, Thailand, and Vietnam, who have similar at-risk populations in order to share our results. We plan to share results at international conferences and through peer-reviewed journal article publications.

### Potential risks and benefits

#### Human participants

This study will involve human participants and their protection is in accordance with the NECHR and the Touro College Institutional Review Board. NECHR reviews research proposals involving human participants with a view to safeguard the dignity, rights, safety, and wellbeing of all actual or potential research participants. They state that the goals of research, however important, should never be permitted to override the health and wellbeing of the research individuals. The Touro College Institutional Review Board aims to protect the rights and welfare of human participants recruited to participate in research activities conducted under the auspices of the College. The Board is registered with the federal Office of Human Research Protections (OHRP) and received approval of its Federal Wide Assurance (FWA) on 30 April 2008.

All key personnel involved in this study will be required to complete the online National Institute of Health (NIH) course on the protection of human research participants and to show proof of course completion which will be kept on file. No research or recruitment of individuals will begin without approval of the two ethical review boards mentioned above.

### Risks to human participants

#### Human participant involvement, characteristics, and design

The focus of this study is to increase the rates of HIV testing and condom use in FEWs because they have been identified as a group that is at-risk for HIV infection. Female young adults who are classified as a vulnerable population comprise most of the study population. Because this study is testing an intervention tailored specifically to females, men will not be eligible to be participants. All recruitment activities and study procedures involving study participants will follow national guidelines. We anticipate involving a minimum of 600 FEWs in the study, and our sampling strategy will ensure that the group of participants is representative of the total population of young FEWs in Cambodia. Assigning study arms will be done at random, meaning that all participants have an equal chance of being assigned into the two active arms or the control arm. They will not be masked to the intervention since the intervention involves receiving SMS/VMs on their mobile phones.

#### Sources of materials

As stated in the study protocol, research materials will include interview digital audio files and transcripts, field observation notes, survey responses, and SMS/VM response data. All data obtained through FGDs, in-person questionnaires, or SMS/VM data collection will be de-identified and stored in password-protected electronic files as well as in a hard copy format in locked file cabinets at the KHANA’s office in Cambodia and at Touro University California and will only be accessible by the Principal Investigators and Co-Investigators.

#### Potential risks

The risks to participation in this study include psychological distress as a result of answering questions about sensitive subjects and a breach of confidentiality as a result of receiving the SMS/VMs about sensitive topics on their mobile phones. This may put participants at risk of negatively affecting their occupational, personal, or romantic relationships if someone else sees the messages. For those participating in FGDs, there may be an infringement on privacy if participants feel pressured or get caught up in the moment and disclose personal information to people they may know or see in their workplaces or communities. To address these risks, all study participants will be informed about the voluntary nature of their participation and their rights to end the participation at any point during the study without any consequences. They will have access to free youth-friendly counseling services and will also be given information about crisis centers and other relevant referrals, and they will be offered escorted referrals.

### Adequacy of protection against risks

#### Recruitment and informed consent

Participants will be recruited by community health workers. Before participation in any study activities, a verbal consent will be sought from the study participants. Data collectors will sign the consent form to confirm that the study participant has been briefed about the study, assured of their confidentiality, and have given their informed consent to participate in the study. Study participants will also be informed of the option for escorted referrals to appropriate existing government and non-government services in the province if they so wished. Because this research topic is highly stigmatizing, verbal consent is the most appropriate form of consent so that no other identifying information is collected. For those study participants who cannot read, we will identify individuals who work in the outreach programs but are not part of the research team to act as witnesses and to sign the consent form.

#### Risk for vulnerable groups

We will be enrolling vulnerable populations and participants who may be pregnant or become pregnant during the study. Pregnancy does not exclude participants from the study but is not the target group of this research. All activities with these groups meet the procedural guidelines of our institutional review board. There are no known risks to the health of pregnant women or their fetuses or neonates of participating in this study. In addition, there may be benefits to them because FEW-specific SRH services will be made available to them throughout the study period, and trained community health workers will offer them free escorted referrals to SRH services.

#### Confidentiality and data monitoring

The records of this study will be kept confidential. The research team will not include the name or personal identifiers of any participants involved in the research in our reports. The interview recordings, questionnaires, and recordings obtained from the participants will be safely locked away in a digital recorder with a passcode. Electronic transcripts will be stored on a password-protected laptop. Informed consent forms and demographic questionnaires with identifiable information will be stored in a locked bag during transportation to and from the study sites. These forms will be kept in a separate locked file away from digital recordings and transcripts. The research coordinator is the only person who will have access to these records.

Data monitoring and interim analyses at the six-month and one-year follow-up will be conducted by the lead investigators of the research team. At that time, the team will determine if the trial should be continued as planned, stopped early for hazard (including social harms), or stopped early because efficacy is overwhelmingly established or the trial is futile.

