### Participant selection criteria

All participants must: (1) work at an entertainment venue in the selected study sites; (2) be currently sexually active defined as having engaged in oral, vaginal, or anal sex in the past three months; (3) own a mobile phone; (4) know how to retrieve VM or retrieve and read SMS on a mobile phone (Khmer or Romanized Khmer); (5) self-identify as a FEW; (6) be willing to receive two SMS/VM per week for one year; (7) provide a written informed consent; and (8) agree to a follow-up visit after six months and 12 months. Figure 1 depicts participant flow diagram for the study.

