### Sampling and participant recruitment

We will use a stratified random sampling method to recruit survey participants. Venues will be selected from a list of all entertainment venues in the study sites based on a recent report on geographic information system (GIS) mapping of HIV key populations in Cambodia [47]. They are matched with 30 similar venues and then randomized for size and type of the venues. We will continue to sample from our list of all entertainment venues until we have a total of 600 FEWs recruited. All enrolled participants will complete an informed consent and a baseline questionnaire survey. Next, one venue from each venue pair will be randomly assigned to the intervention group: VM or SMS (1) and the other to the control group (0) with standard of care (no additional mobile phone-based SRH support) with a 1:1 venue allocation ratio. Both groups will be followed for one year, and a six-month and 12-month questionnaire will be administered by trained data collectors (see Fig. 3).

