#### Phase II: Intervention

The *Mobile Link* intervention comprises a series of automated SMS/VMs to participants’ mobile phones over the 12-month period. Participants will receive the first message within the first day of the intervention. The messages will be designed to enhance and increase utilization of existing HIV and SRH services by reminding clients about safe sex methods available to them and providing a conduit for additional support. Upon enrollment into the study, participants in all groups will receive a face-to-face baseline behavioral survey conducted by a data collection team who remained masked to intervention allocation at enrollment.

The baseline questionnaire (see Additional file 5) was designed by the study team using sections from standard questionnaires currently in use at KHANA for assessing similar measures in populations of high-risk women in Cambodia. The questionnaire was created in English, translated to Khmer, and back-translated to English. The questionnaire will be pilot tested with 15 FEWs similar in eligibility to future study participants using cognitive interviewing techniques [48]. Next, participants will be randomized into intervention and control groups: Group 0 is the control group and Group 1.1 and 1.2 are the intervention group (1.1 = SMS [1.1a Khmer characters or 1.1b Romanized Khmer] or 1.2 = VM in Khmer).

Those in the control group will get one “check-in” SMS or VM between baseline and midline and another between midline and endline. Participants will be asked to confirm receipt of this message. These messages will contain no health information and will be used as a way to stay in touch with participants and to compare “receipt confirmation” rates to the intervention group. All participants will be asked to choose whether they would prefer to receive SMS or VM and their reason for their choice. If they choose SMS, they will be asked if they prefer Khmer characters or Romanized Khmer. Recent studies on choosing the method for receiving interventions during an RCT have demonstrated that it may increase participation and retention [49].

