A message schema was developed in which each participant will receive a message from a different topic group each week for 10 weeks. The messages will tend to follow a flow of rights-based health information and then linkage (though there is some variance depending on topic). However, after each message, participants will also have the option to be linked to an outreach worker. After the tenth week, the topic areas will cycle through again, but the messages within the topic areas will be unique. After weeks 30, 40, and 50 (+ 2), messages will be repeated to reinforce particular concepts and ideas. Participants who indicate they would like to talk to a counselor will receive a call from a *Mobile Link* staff. The counselor will provide individualized information via telephone or face-to-face on that particular topic and, if needed, can escort the participant to receive the required services.

Participants will also receive a weekly 5–7-question survey that asks about more common and/or time-sensitive issues such as STI symptoms, vaginal infection/irritation, support for GBV, or psychological issues. Once a month, participants will be asked if they are using contraception and/or want to be linked to family planning counseling. Participants who endorse any of the survey questions will be asked if they want to be linked to an outreach worker. Therefore, it is important to note that, while the topics in the messages will change each week—as well as the topical prompts for linkages to outreach workers—the weekly monitoring survey provides another consistent and constant platform for mobile linkage.

Trained data collectors and community health workers in the selected sites will deliver the *Mobile Link* intervention. SMS/VM are scheduled and sent using the open-source software program developed by InSTEDD (instedd.org). InSTEDD and the Project Coordinator will retain data on the SMS/VM messages sent, responses to messages, and outcomes of follow-up phone calls.

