### Data collection

Data collection tools will include baseline and follow-up questionnaires administered by a data collection team. The baseline questionnaire will contain questions to collect information on contact details; demographics; pathways to entertainment work; information about their current workplace; SRH knowledge, attitudes, and behaviors; sexual relationships; condom use self-efficacy; and experiences with GBV. All questions will be asked in both written and oral forms because literacy rates are not 100% in this community. In addition, all data collected via weekly monitoring surveys will be analyzed on a routine basis.

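### The one-year hazard decision cannot stop messaging for a woman who has reached it; the six-month look, at about half of her contacts, is the only stated one that can act for her

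*Protocol article*

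**What the plan says.** Under Confidentiality and data monitoring, the lead investigators carry out monitoring and interim analyses at two times, six months and one year. The hazard decision is tied to those times: "At that time, the team will determine if the trial should be continued as planned, stopped early for hazard (including social harms". The sentence then adds stopping for efficacy and for futility, which are not at issue here.

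The length of exposure is stated in several places:

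- Participant selection criteria: a woman must "be willing to receive two SMS/VM per week for one year".
- Sampling and participant recruitment: "Both groups will be followed for one year".
- Phase II: Intervention: automated messages go to participants' "mobile phones over the 12-month period".
- The same section describes a schema in which "each participant will receive a message from a different topic group each week for 10 weeks", after which the topics cycle. It closes with: "After weeks 30, 40, and 50 (+ 2), messages will be repeated to reinforce particular concepts and ideas". A weekly monitoring survey runs alongside.

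Harm information is also handled elsewhere. Ethical consideration says that surveys ask about social harms and that investigators record and follow the harms reported to staff. It also lets women leave the study whenever they wish and links those harmed to services. Phase II: Intervention says that "the Project Coordinator will retain data on the SMS/VM messages sent, responses to messages, and outcomes of follow-up phone calls". Data collection says that "all data collected via weekly monitoring surveys will be analyzed on a routine basis". None of these places names a time or an action for a trial-level stop.

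**The concern.** A hazard stop protects participants only while there is exposure left to stop. Here the exposure is the messaging itself. Potential risks names loss of confidentiality when someone else sees a sensitive message, with damage to work or relationships. Ethical consideration foresees an argument or violence when a voice message is overheard. Any message can lead to such an event, from the first week to the last.

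Of the two decision times in the text, one falls where messaging ends and the other at its midpoint. If harms built up during the first months or the second half, the stated plan names no point in those periods at which someone must decide whether messaging goes on. What is at stake is the timing of a protective decision for a group that the article itself calls vulnerable. No estimate or error rate is affected.

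**Working it through.** The article gives no figure for the share of contacts delivered by each look, so there is none to reproduce. The check is exposure arithmetic for one intervention-arm woman whose messages start at enrolment.

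**Inputs from the article**
- Contact rate: two per week for a year (Participant selection criteria). This fits one topic message plus one survey per week (Phase II: Intervention).
- Duration: 12 months, taken as 52 weeks. The schema ends at week 50 + 2 = 52.
- Decision times: six months (week 26) and one year (week 52).

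**Formula:** share delivered by week t = (rate × t) / (rate × 52) = t / 52. The rate cancels, so the percentages do not depend on which contacts are counted.

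**The stated looks**
- Two per week: total 2 × 52 = 104. By week 26, 2 × 26 = 52, or 50%. By week 52, 104, or 100%, with 0 left.
- Topic messages only: total 52. By week 26, 26, or 50%. By week 52, 52, or 100%, with 0 left.

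**Staggered enrolment.** The article gives no recruitment length, so these are assumptions: R = 0, 3 or 6 months of even enrolment.
- A six-month look that waits for the last enrollee comes after (6 + R)/12 of the first enrollee's contacts: 50%, 75% or 100%. The mean over women is (6 + R/2)/12: 50%, 62.5% or 75%.
- A one-year look taken when the first enrollee reaches 12 months leaves R/12 of the last enrollee's contacts: 0%, 25% or 50%. The mean over women is R/24: 0%, 12.5% or 25%.
- A one-year look taken when the last enrollee reaches 12 months leaves 0% for everyone.

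**Delayed start.** If messaging began 2 to 8 weeks after baseline (assumed) and the year were counted from baseline, 4 to 16 of 104 contacts would remain at one year.

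**With quarterly review and a common start**
- Reviews at weeks 13, 26 and 39 fall after 26, 52 and 78 of 104 contacts: 25%, 50% and 75%.
- Contacts still open to the first decision: (104 − 26)/104 = 75%, against (104 − 52)/104 = 50% now.
- Longest interval between decisions: 26 contacts (13 topic messages), against 52 (26 topic messages) now.

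These figures describe timing of exposure only. No harm rate is assumed, so they do not convert into a number of women protected.

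**The case against.** The strongest reply is that harm oversight already runs throughout. Investigators follow reported harms, weekly survey data are analysed routinely, women are repeatedly offered an outreach worker, and anyone can withdraw. The investigators who follow harms overlap with those who take the hazard decision. A reader might infer that hazards would go unaddressed for six months, or that a stop between looks is ruled out. The documents support neither: the monitoring section does not say that a stop may be made only at those two times. What remains is narrower. The one-year decision is misplaced for women who have reached it, and the running surveillance is not tied to a decision.

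It can also be said that a journal article leaves between-look safety procedures to the full protocol. That is fair, and the absence of a detailed schedule is not the complaint. The one-year placement is something the article itself fixes.

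Four limits stand:

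- The counts apply to the intervention arm. Control women receive no health messages, and their check-ins carry no health content, so the disclosure risk is mainly on the other side.
- A reader might infer that the one-year look can protect nobody, or that early enrollees will be 75% to 100% through before the six-month look. Both depend on recruitment length and on what triggers each look, which the article does not give. The statement about waiting for six-month follow-up to be complete, in Analyses of primary and secondary outcomes, concerns the outcome analysis and may not govern the hazard look.
- If the survey question on social harms is asked only face to face, an early review would hold mainly staff reports, call outcomes and reasons volunteered at withdrawal. The share of contacts still open is then an upper limit on what a review could influence. The one-year flaw holds on either reading.
- Withdrawal and referral help the individual woman, usually after the event. They do not replace a decision that protects the others.

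**Conclusion.** The point holds in this limited form. One of the two stated hazard decisions cannot stop exposure for any woman who has reached it. The other comes after about half of an intervention-arm woman's contacts (52 of 104, or 26 of 52 topic messages) and is the only stated one that can act for her. This rests on messages starting at enrolment and running 52 weeks; the 50% does not depend on the contact rate. Under staggered enrolment, an early-triggered one-year look could still spare late enrollees some messages, but the article states no such trigger.

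The gain from correcting it is minor to moderate. The article judges adverse effects unlikely, and surveillance, withdrawal and referral continue throughout. The change is still worth making, because it is cheap and lets a safety decision act while messages are being sent.

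**What to change.** Amend Confidentiality and data monitoring along these lines:

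*While any woman is receiving messages, the lead investigators will periodically (for example quarterly, and in addition at six months) review a cumulative, de-identified tabulation of the social harms reported under Ethical consideration. At any of these reviews, or whenever a serious harm is reported, they may pause, change or stop messaging. The one-year look is the final harm summary.*

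The tabulation can draw on data already held: staff reports, survey replies, call outcomes and reasons given for withdrawal. It is descriptive, so it spends no alpha, and the blinded data collectors need not see it. No new question is needed. If one is added, it should be asked by live contact when the woman can talk privately, because phones may be shared. The interval and the level of harm that should halt messaging are for the investigators and the ethics committees; quarterly is only an example.

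Cost: protocol wording and a little time from existing staff. With a common start, quarterly review adds two tabulations (weeks 13 and 39). With an assumed 3 or 6 months of enrolment, messaging spans 65 or 78 weeks, which is 65/13 = 5 or 78/13 = 6 quarterly points. Less the two looks already planned, that adds about three or four.
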